### Sample size calculation

As no study has yet defined the minimal clinically important difference for HR reduction in POTS, we consider the results of Stavrakis *et al*^20^ to be clinically relevant and have therefore used them as the basis for our sample size calculation. In addition, in the absence of direct clinical data on the effect of slow breathing training on POTS, we assumed an additional reduction from slow breathing training based on studies showing that slow breathing training can reduce HR by approximately 4–10 bpm in various cardiovascular conditions.^34 39 40^ We have used a conservative estimate of seven beats per minute, which we believe to be a minimal clinical difference. This reduction represents not only a measurable physiological change but may also contribute to psychological well-being, as studies suggest.^41^ For our clinical trial investigating the effects of AVNT with and without breathing training and a sham AVNT intervention, we calculated the required sample size based on expected HR changes (ΔHR). This calculation was performed for an analysis of variance using HR data from Stavrakis *et al*^20^ and incorporating an assumed reduction of 7 bpm from slow breathing. Although Stavrakis *et al*^20^ reported no significant reduction in HR in the sham AVNT group, we conservatively assumed a placebo-related reduction of 2 bpm for both sham conditions to account for potential expectancy effects.

We estimated the following mean ΔHR values across the four groups:

AVNT with NB: 17.6 bpm (as reported by Stavrakis *et al*)^20^AVNT with slow-paced breathing: 10.6 bpm (17.6–7 bpm)Sham AVNT with slow-paced breathing: 22.7 bpm (placebo-adjusted 2 bpm reduction from 31.7 and 7 bpm reduction from slow-paced breathing)Sham AVNT with NB: 29.7 bpm (placebo-adjusted 2 bpm reduction from 31.7 bpm)

Assuming an SD of 14 bpm, an alpha level of 0.0167 (Bonferroni correction for 3 pairwise comparisons across four groups), and a power of 80%, 17 participants per group are required for sufficient statistical power. To account for an anticipated 30% dropout rate, 25 participants per group will be recruited, resulting in a total sample size of 100 participants.

Sample size was computed using the University of Vienna’s online analysis of variance (ANOVA) calculator: https://homepage.univie.ac.at/robin.ristl/samplesize.php?test=anova

### Recruitment

We are recruiting participants for our study through various channels. First, we are working closely with support groups such as Long COVID Austria (https://longcovidaustria.at/). We are also using online platforms like POTS-Dysautonomia.net to reach individuals actively seeking information and support for POTS. Additionally, we collaborate with [name], recognised as one of Austria’s leading experts on postacute infection syndrome. Through his numerous TV and radio appearances, he is an important advocate for people with POTS and has an extensive network within the healthcare community. His strong media presence and expertise significantly enhance our ability to identify potential POTS patients.

To ensure successful recruitment for this RCT, we intend to implement the following measures:

Recruitment tracking and strategy adjustment

We will maintain detailed records of all individuals screened, including those deemed eligible and enrolled.A monthly review of recruitment progress will be conducted to identify and address any challenges early and make any necessary adjustments to our strategy.Recruitment sources will be continuously analysed (eg, online platforms, physician referrals) to identify the most effective channels and allocate resources accordingly.If necessary, we will refine our recruitment methods and eligibility criteria to ensure that we reach the target population for the study.

Thorough eligibility assessment

We will systematically document reasons for participant ineligibility to identify common exclusion factors and refine our recruitment strategy as necessary.Regular review of the inclusion and exclusion criteria will ensure that they are appropriately representative of the target study population.

Participant engagement:

We will ensure clear and transparent communication of study expectations to build trust and encourage participant engagement.Regular check-ins will be scheduled to maintain participant engagement throughout the study.We will proactively address any participant concerns or questions to minimise attrition.

Feasibility report:

At the end of the recruitment phase, we will produce a detailed report summarising successful strategies, challenges encountered and key lessons learnt.This information will be used to optimise recruitment strategies for future clinical trials in POTS or similar populations.

### Randomisation and blinding

#### Sequence generation

The random allocation sequence will be generated using the Good Clinical Practice (GCP)-compliant, web-based Randomizer service provided by the Medical University of Vienna. This system uses a computer-generated randomisation algorithm to ensure allocation by chance and adherence to GCP standards.

#### Type of randomisation

Stratified block randomisation with a 1:1:1:1 allocation ratio will be used across the four study groups: AVNT+SDB, AVNT+NB, sham AVNT+SDB and sham AVNT+NB. Randomisation will be stratified by PEM status (yes/no), resulting in two strata. The precise block sizes and restrictions are programmed within the Randomiser system but remain undisclosed to the investigators to minimise predictability.

Sex distribution will be monitored throughout recruitment and reported descriptively. Given the expected limited number of male participants, additional stratification by sex was not implemented, as this could result in small and unstable subgroups. However, sex will be considered in the statistical analysis as a covariate or explored in sensitivity analyses, where sample size permits.

#### Allocation concealment mechanism

Allocation concealment is maintained by the central Randomiser system. Group assignment remains hidden until a participant is enrolled and confirmed in the database. All randomisation processes are automatically logged and stored as an electronic audit trail, ensuring complete transparency and traceability.

#### Implementation

The study nurse will be responsible for enrolling participants and entering the necessary data into the Randomiser system. Once randomisation is complete, the group allocation will be retrieved. The PhD student/study nurse and the physiotherapist supervising the breathing therapy will be informed of the participant’s allocation to administer the assigned intervention according to protocol. The statistician responsible for outcome analysis will remain blinded to group allocation until the database is locked.

#### Blinded parties

Participants will remain blinded regarding their AVNT group assignment (active vs sham) by using identical Nurosym devices with standard electrode placement. In the sham condition, the device employs a ‘sound-sham’ method, delivering pulsed acoustic signals that mimic the auditory cues of active AVNT but do not induce physiological vagal activation. These measures ensure participants cannot reliably distinguish between active and sham AVNT. Participants cannot be blinded to the breathing interventions, as they must consciously perform either slow deep breathing or NB techniques. The study nurse, responsible for conducting physiological measurements such as tilt testing and administering questionnaires, cannot be blinded to the intervention group, as she also supervises daily AVNT sessions and directly observes the breathing exercises. To reduce bias, all data will be coded, and the data analyst (statistician) will remain blinded to group allocations until the primary analyses are complete. Unblinded personnel thus include the physiotherapist delivering the breathing training and the study nurse supervising daily AVNT sessions. Outcome assessors and data analysts will remain blinded.

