### Eligibility criteria for sites and individuals

Since this is a single-centre trial conducted at the Medical University of Vienna, no additional site-specific eligibility criteria are necessary. The trial will take place in the autonomic laboratory of the second Department of Medicine with Cardiology and Intensive Care Medicine at Clinic Landstrasse. Assessments, including physiological testing and data collection, will be performed by a trained study nurse with expertise in autonomic and cardiovascular assessments. The breathing therapy intervention will be administered by a licensed physiotherapist with over ten years of experience in respiratory and autonomic rehabilitation.

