### Intervention and comparator

Before starting the intervention, all participants attend a 60-minute introductory training session led by a physiotherapist experienced in respiratory and autonomic therapy, where the correct use of the device, electrode placement and adherence strategies are covered. The first stimulation session is carried out under supervision to ensure proper application and participant safety.

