Supine phase—autonomic assessment (approximately 20 min total)The examination begins with a brief calibration phase of 2–3 min, during which all monitoring devices are calibrated and signals optimised, including finger-cuff BP system calibration.Once stable signals are confirmed, RSA is assessed using a standardised paced-breathing protocol. Participants are first familiarised with the breathing technique for 1 min using a visual pacer, then asked to maintain a breathing rate of 6 breaths per minute (0.1 Hz: 5 s inhalation, 5 s exhalation) for 2 min while ECG, beat-to-beat BP and EtCO₂ are recorded continuously. After completing the RSA assessment, participants return to spontaneous breathing and rest for 3–5 min to allow cardiovascular parameters to stabilise. Following this recovery period, a 10 min baseline recording is obtained while participants breathe spontaneously and remain still. This entire 10 min baseline phase is used for analysis to ensure optimal signal stability before proceeding to the tilt phase.Throughout the entire supine phase, HR (ECG), beat-to-beat BP and EtCO₂ are recorded continuously. Event markers are set to delineate the different assessment phases for subsequent analysis.Upright phase HUTT (15 min or until termination)Following the supine baseline, the tilt table is moved from horizontal to 70° within a few seconds and maintained in the upright position for 15 min or until intolerance occurs. Throughout the tilt phase, all haemodynamic parameters (ECG, beat-to-beat BP, EtCO₂, SpO₂) are recorded continuously. Symptoms will be documented using the Vanderbilt Orthostatic Symptom Score (VOSS),^28^ which evaluates nine orthostatic symptoms on a scale of 0–10.The VOSS is administered at the 10-minute mark or immediately on test termination. Additionally, the examiner continuously documents the type, onset time, and severity (0–10) of any newly occurring symptoms throughout the upright phase. The test is terminated early in case of syncope, presyncope, severe symptomatic hypotension, participant request or other medical concerns.

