**ΔHR=mean HR during the 10-minute upright phase−mean HR during the 10-minute supine baseline**

#### Secondary outcomes

BP: Continuous beat-to-beat BP readings will be obtained using a non-invasive finger-cuff system and summarised into 1-minute averages. Additionally, brachial oscillometric BP measurements will be performed at baseline and every 3–5 min for calibration and verification. The outcomes include changes in ΔMAP, ΔSBP and ΔDBP, defined as the mean values during the 10-minute upright phase minus the mean values during the 10-minute supine baseline period. Additional outcomes include the presence of orthostatic hypotension according to predefined thresholds and initial orthostatic responses, such as the nadir SBP within the first 30 s after tilt-up and the time to recovery.

RSA: RSA is quantified as an index of cardiovagal parasympathetic function using the CNSystems Task Force Monitor (CNSystems Medizintechnik, Graz, Austria). RSA amplitude (ΔHR) is calculated using the peak-to-valley method, which determines the difference between maximum HR during inspiration and minimum HR during expiration for each breathing cycle, then averaged across all cycles during the 2-minute paced-breathing period, and expressed in beats per minute (bpm). Values are interpreted considering established age-related and sex-related variations in RSA.^29^

Breathing assessments: Symptoms of dysfunctional breathing will be assessed using the NQ, a validated 16-item self-report instrument. Items are rated on a 5-point Likert scale (0–4), yielding a total score of 0–64, with higher scores indicating greater symptom burden; scores ≥23 suggest clinically relevant hyperventilation syndrome. The NQ is widely used as a screening tool in clinical populations.^30^ In addition to self-report, breathing patterns will be assessed using the BPAT, a validated observational tool. A trained assessor will evaluate key features of dysfunctional breathing at rest, including thoracic versus abdominal movement, chest wall symmetry and use of accessory muscles. Items are scored based on severity and summed to provide an overall index of breathing pattern disturbance.

The BPAT has been shown to be a reliable clinical tool for identifying dysfunctional breathing patterns and is suitable for use in both research and clinical practice.^31^

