### Data collection methods

All data will be collected following standardised operating procedures to ensure validity, reproducibility and compliance with GCP. Physiological assessments, including tilt testing, ECG, BP, RSA and capnography, will be conducted by a trained study nurse in accordance with the predefined test protocol. The study nurse will receive specific training in autonomic testing and laboratory safety before the trial begins to ensure consistent assessment practices. Patient-reported outcomes will be gathered using validated and widely recognised questionnaires: the NQ, BPAT, MAPS, SF-12, CFS, HADS. Questionnaires will be provided either in paper format or digitally, depending on participant preference and health condition. To improve data quality, the study nurse will perform immediate plausibility checks of recorded measurements and questionnaires after each visit. All data will be documented in electronic case report forms via REDCap. Range checks and automatic validation rules will be implemented to minimise data entry errors. Paper forms will be available as a backup in case of system failure and will be double-entered into REDCap as soon as possible.

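### The section on blinded parties says the nurse who runs the tilt tests is unblinded, then says outcome assessors stay blinded; for the primary endpoint both cannot be true

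*Protocol article*

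**What the plan says.** All references are to the protocol article.

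- Blinded parties: the study nurse conducts the tilt tests and administers the questionnaires, and she "cannot be blinded to the intervention group, as she also supervises daily AVNT sessions and directly observes the breathing exercises". She is then named with the physiotherapist as unblinded personnel. The section ends: "Outcome assessors and data analysts will remain blinded".
- Implementation: the PhD student/study nurse and the physiotherapist "will be informed of the participant’s allocation to administer the assigned intervention according to protocol".
- Data collection methods: "Physiological assessments, including tilt testing, ECG, BP, RSA and capnography, will be conducted by a trained study nurse".
- Eligibility criteria for sites and individuals: "Assessments, including physiological testing and data collection, will be performed by a trained study nurse".
- Secondary outcomes: one further assessor appears, for the breathing-pattern rating (BPAT), without a named role: "A trained assessor will evaluate key features of dysfunctional breathing at rest".

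**The concern.** Whether the person measuring the primary endpoint knows the treatment is one of the first things a reader looks for when judging risk of bias. Here the same section gives two answers. Someone who relies on its closing sentence would record the tilt assessor as blinded, when the preceding text says she is not. The list of strengths and limitations does not correct this: it mentions that the breathing intervention cannot be blinded, but not that the tilt assessor is unblinded.

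The stated reason also needs a second look. If the nurse really attends daily stimulation, her unblinding is hard to avoid. If daily use is mostly at home, the active/sham part of her knowledge might be avoidable.

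**Working it through.** No arithmetic decides this point; the sections have to be set side by side.

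**1. Who measures the primary endpoint?** ΔHR comes from the tilt test (Primary endpoint, Procedure). Data collection methods and Eligibility criteria for sites and individuals both give that test to a study nurse. The BPAT rater is the only other assessor mentioned, and that rating is not part of ΔHR. The section Trial monitoring speaks of study nurses in the plural, but only for internal monitoring. No section assigns a second, blinded nurse to the tilt.

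**2. Does she know the allocation?** Yes, on two counts: Blinded parties says she cannot be blinded, and Implementation says she is told.

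**3. Can the closing sentence still be true?** For the data analyst, yes. For BPAT, possibly, if the unnamed rater is someone else. For the tilt test, no.

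**4. Does the rest of the document bear out daily supervision?** Blinded parties states it twice. Other sections describe a lighter arrangement:

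- Intervention and comparator: "The first stimulation session is carried out under supervision to ensure proper application and participant safety". No later session is described as supervised there.
- Diaphragmatic breathing: a weekly diary sent through the app.
- Strategies to improve adherence: daily use logged by app, with follow-up every 2–3 weeks by phone or in person.
- Plans to promote participant retention and follow-up: nurse calls at weeks 2, 6 and 10, that is, three calls in 12 weeks.

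This is tension rather than contradiction. App logs and calls do not rule out supervision, and no section says that participants treat themselves unsupervised.

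**5. How could her knowledge reach the outcomes?** ΔHR is a difference of two means from continuous ECG, so reading error is not the main route. What remains is how the test is run and when it is stopped: "The test is terminated early in case of syncope, presyncope, severe symptomatic hypotension, participant request or other medical concerns". The last two grounds leave some room for judgement. The tilt lasts 15 min and the endpoint uses a 10-minute upright phase. If that means the first 10 minutes (an assumption), only a stop before minute 10 shortens the averaged window. The examiner also records the type, onset and 0–10 severity of new symptoms, which depends directly on her judgement.

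**6. Scope.** Planned week-12 tilts: 4 × 25 = 100 if everyone attends. If all of the planned 30% dropout missed the test: 100 × (1 − 0.30) = 70. The second figure is a low case, because participants who stop the intervention are encouraged to stay in follow-up. Both figures assume that the baseline tilt precedes disclosure of the allocation and that there is no intermediate tilt; the schedule figure is not available to check this.

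**7. Could the active/sham code be kept from her?** Active and sham devices are described as identical, and a physiotherapist who is already unblinded leads the device training. The obstacle is intensity setting: active stimulation is adjusted to a felt tingling, while the sham delivers no current, so whoever sets it can infer the arm. The breathing arm cannot be reliably hidden from her.

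**The case against.** The protocol does not hide the unblinding. It states it twice before the closing sentence and calls the trial partially blinded, so only a reader who takes that sentence alone is misled. This is fair, and it means that correcting the sentence cures the misstatement. It does not make the sentence true.

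The consequence for ΔHR is limited. The endpoint is an ECG mean under a predefined test protocol, syncope and presyncope leave the examiner little discretion, questionnaires are self-completed, and secondary p values are exploratory. All of this stands and bounds the point.

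A reader might infer that the daily-supervision reason is simply false and should be struck out. The document does not support that. Blinded parties asserts it twice, Implementation gives the nurse a part in administering the intervention, and in-person follow-ups are allowed. Thin corroboration in a condensed article is a reason to ask, not proof of error.

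Finally, withholding the code rests on facts not given. The devices are called identical in the context of participant blinding; nothing says they carry codes or that staff cannot tell them apart, and the physiotherapist's capacity is not stated. That part is therefore a preference subject to feasibility.

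**Conclusion.** The contradiction is certain: for the primary endpoint, the document claims a blinded outcome assessor that its own arrangements do not provide. It should be corrected. A reader might go further and conclude that ΔHR will be biased by a material amount; the document gives no basis for any size, and none is claimed. The exposure is every post-allocation tilt, 70 to 100 tests at week 12 under the assumptions shown, acting on ΔHR mainly through test conduct and discretionary early stopping, and more directly on examiner-recorded symptoms. The reason given for unblinding the nurse needs clarifying but stands until the investigators say otherwise.

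**What to change.** **Minimum, at almost no cost.** Replace the closing sentence of Blinded parties with: *The tilt assessor is unblinded; only the data analyst is blinded.* If the BPAT rater is a different and blinded person, say so separately. State what daily supervision by the nurse means in practice. Report the unblinded tilt assessor as a limitation, noting that the effect on ECG-derived ΔHR is limited mainly to test conduct and discretionary early termination, and that examiner-recorded symptoms are also exposed.

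**Preferable, if feasible, for participants not yet randomised.** Have the physiotherapist retrieve the AVNT allocation, issue the device and set the intensity. Withhold the active/sham code from the nurse who runs the tilt. Record her guess of the AVNT arm at the week-12 tilt, alongside the participant questionnaire already planned under Unblinding procedures. The closing sentence would then say that the tilt assessor is blinded to active/sham AVNT only, not to the breathing arm.

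**Cost of the second option.** A small shift of tasks to the physiotherapist and a change in access to the Randomiser system. Enrolment began on 19 March 2026, so this needs an ethics amendment (Protocol amendments), and assessor blinding would differ between earlier and later participants, which has to be reported. Some leakage through participant contact will remain; the recorded guess shows how much.

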#### Unblinding procedures

Unblinding will only occur if medically necessary, for example, in the event of a SAE where knowledge of treatment allocation is essential for participant safety. Any unblinding will be documented, including the reason, time and person responsible. At the conclusion of the trial, participants from all study arms will be asked to indicate via questionnaire which intervention they believe they received and their level of certainty. This assessment will allow evaluation of the success of blinding.

